**Discussion:**

This study will be conducted on a cohort of 40 students from a reputed Health Sciences College, UAE, to evaluate the integrity of a proposed AI comentoring model for monitoring academic performance throughout a semester. The AI models (supervised and segmentation engines) will be tested at two time points: the 5th and 10th weeks. At each time point, categorized student performance data will be uploaded to the AI platform, based on pedagogical parameters, and used to generate a personalized text draft automatically (local pseudonymization + institutional mail merge workflow). To assess the integrity of the used AI, the investigator will perform a manual evaluation of each student's risk status at both checkpoints, alongside statistical analyses. If successful, the system may alleviate the workload of human mentors, enable timely interventions for at-risk students, and enhance overall student performance and retention.

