### AI-assisted assessment framework

The AI component consisted of an unsupervised machine learning–based clustering module designed to group students according to multidimensional performance indicators derived from assessment artifacts (e.g., rubric scores, task completion metrics, and structured feedback variables). No outcome labels or performance categories were predefined, and the algorithm did not generate pass/fail or diagnostic classifications. Clustering outputs were interpreted as exploratory competency profiles intended to support sensemaking and reflection, rather than automated judgment. The AI system functioned strictly as a decision-support tool, with all summative decisions retained by faculty.

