### Data processing

This pilot feasibility study focuses on a single group of students from the Bachelor Program at College of Health Sciences (CoHS), GMU, with a minimum sample size of 40 participants to assess the feasibility and acceptability of the approach. Given the pilot sample size (*n*=40), model evaluation will use repeated stratified k-fold cross-validation (or leave-one-out CV) and bootstrap confidence intervals to reduce instability from fixed splits. A pre–post analysis will be conducted to evaluate the significance of differences in the occurrence of high-risk students at each stage of data collection (across three time points). The third assessment point will be their final score and passing percentage. Subsequently, this study may be expanded to a larger sample size using a cluster-randomized group study design. The project will utilize Python and related libraries.

Additional automated alerts and academic advice generated by AI will be thoroughly cross-verified by the investigators with respect to the target students and mentors. In parallel, the investigators will manually analyze student performance using data from the three designated time points [human-in-the-loop governance (mentor approval and escalation)]. This process will allow the investigators to confirm the integrity, accuracy, and functionality of the newly proposed AI mentorship model. A survey will also be conducted among the targeted students and faculty to assess their responses, success rates, and the accuracy of the proposed AI co-mentoring model in tracking academic progress. The present study is designed to use quantitative data, while qualitative data from the survey will be used for validation purposes. Figure 1 provides an overview of the intended workflow in the form of a flowchart.

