#### Interpretation framework

Analytic results were interpreted within a decision-support paradigm, recognizing faculty assessment as the reference standard and AI outputs as supplementary insights. Statistical findings were used to characterize alignment patterns rather than to adjudicate correctness or automate evaluative decisions.

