Feasibility challenges such as data quality, technical limitations, and the risk of systemic errors will be mitigated through model fine-tuning and human oversight via face-to-face mentoring where needed. Participants will be informed of potential errors issues with AI mentoring, if any, in advance to prevent confusion or panic. A glossary of key terms is appended in Table 7.

**Table 7 T7:** Glossary of key terms.

Term	Definition
AIAS (AI Risk Identification Assistance System)	The AIAS refers to a system in which artificial intelligence tools are used to support and enhance human decision-making or analysis, with final judgment and control remaining with the human user.
Supervised model	A predictive model trained on historical student data with known outcomes, used to classify future student risk.
Unsupervised model	A model that identifies patterns or clusters in student data without prelabeled outcomes, used to detect groups of students with similar risk profiles.
Risk report	A structured summary of a student's likelihood of academic difficulty, including risk labels and recommended support actions.
Human validation	The process by which trained evaluators independently review and confirm risk status, ensuring AI-generated outputs align with expert judgment.

In conclusion, this pilot feasibility study not only explores the comparative strengths of supervised and segmentation engines in risk prediction, but also contributes to the ongoing development of effective validated AI-assisted mentoring systems focused on pedagogy and academic performance outcomes. The study findings are expected to provide critical insights into the practicality, reliability, and impact of integrating AI into student support services and lay the groundwork for future large-scale implementations across educational institutions. Each assessment component has been already mapped to the course learning outcomes.

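### Human risk ratings are not kept blind to the AI output, so AI–human agreement may be biased upward by an unknown amount

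*Protocol article*

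**What the plan says.** All references are to the protocol article.

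- **Investigators check the AI.** Under Data processing, alerts and "academic advice generated by AI will be thoroughly cross-verified by the investigators with respect to the target students and mentors".
- **Investigators also rate the students.** The same paragraph continues: "In parallel, the investigators will manually analyze student performance using data from the three designated time points". Its stated purpose is: "This process will allow the investigators to confirm the integrity, accuracy, and functionality of the newly proposed AI mentorship model". The Discussion part of the Abstract puts this at weeks 5 and 10: "the investigator will perform a manual evaluation of each student's risk status at both checkpoints". These are the points at which the AI receives its data: "At each time point, categorized student performance data will be uploaded to the AI platform".
- **Mentors see AI output.** The text after Figure 1 has a mentor review and approve every message before it goes out. The main Discussion lists agreement with the ratings of human mentors among the things to be determined.
- **Human validation (Table 7)** is defined as: "The process by which trained evaluators independently review and confirm risk status, ensuring AI-generated outputs align with expert judgment".
- **The agreement statistics.** Secondary outcomes and Analysis of secondary outcomes compare AI clusters with categories assigned by faculty, using a confusion matrix, percentage agreement and kappa. The Interpretation framework describes this as "recognizing faculty assessment as the reference standard".
- **AI inputs.** The clustering indicators are "derived from assessment artifacts (e.g., rubric scores, task completion metrics, and structured feedback variables"). Study setting and participants says that the faculty assessors work with structured rubrics.
- **Status.** Agreement is secondary and exploratory, and the statistical sections disclaim any claim of validity.

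**The concern.** Kappa tells how far the AI matches expert judgement only if that judgement was formed without the AI. Two routes threaten this.

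The first is review bias. A rater who has checked an alert, or approved a message that rests on a risk label, may drift toward that label. The second is shared input. If the AI groups students on rubric scores that the faculty themselves gave, part of the agreement reflects common data, including common scoring error, rather than two separate readings of the student.

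Both routes usually push agreement up, and a confidence interval covers neither. This matters because the plan reads kappa for its sign and size and intends the findings to inform larger confirmatory studies. It also cannot be repaired later: once a rater has seen the labels, a blinded rating of that checkpoint is lost.

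**Working it through.** The plan gives no expected kappa, power or effect size, so there is no figure to reproduce. The first step is a reading; the other steps are illustrations on assumed values.

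**1. Who is placed to see the AI output?**

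| Possible human rater | Named as comparator in | Contact with AI output |
|---|---|---|
| Investigators | Abstract (Discussion), Data processing | Verify alerts and advice |
| Mentors | Main Discussion | Approve every message; notified of students below benchmark |
| Faculty assessors | Secondary outcomes, Analysis of secondary outcomes, Interpretation framework | Not stated; not said to be distinct from the other two |

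Two of the three possible raters handle AI output, and the position of the third is open. No section places the rating before the release of the label or blinds the rater. Doing two tasks in parallel says that they run concurrently, not that one is hidden from the other. In Table 7 the word for independence stands in the same sentence as confirming risk status and making AI outputs align with experts.

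**2. Effect of taking over the AI label.** Let k be the blinded kappa and c the share of students for whom the rater takes over the AI label, with category frequencies equal on both sides and unchanged. Observed agreement becomes po + c(1 − po), chance agreement pe stays the same, and so

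observed kappa = k + c(1 − k).

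- k = 0.40: c = 10% gives 0.40 + 0.10 × 0.60 = 0.46; 25% gives 0.55; 50% gives 0.70.
- k = 0.20: the same shares give 0.28, 0.40 and 0.60.
- A check through the agreement table, with assumed categories 60/25/15% and k = 0.50: pe = 0.36 + 0.0625 + 0.0225 = 0.445, and po = 0.445 + 0.50 × 0.555 = 0.7225. With c = 30%, po = 0.7225 + 0.30 × 0.2775 = 0.806 and kappa = (0.806 − 0.445)/0.555 = 0.65. With c = 50%, po = 0.861 and kappa = 0.75.

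**3. Effect of shared scores.** Two three-category ratings (assumed 20/30/50%) were simulated from scores of assumed reliability, with a varying share of error variance in common.

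| Share of error in common | Kappa, reliability 0.7 | Kappa, reliability 0.5 |
|---|---|---|
| None | 0.38 | 0.24 |
| Half | 0.53 | 0.42 |
| Three quarters | 0.66 | 0.57 |
| All (same score, same cut-offs) | 1.00 | 1.00 |

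**4. Comparison with sampling error.** Simple large-sample half-width = 1.96 × √[po(1 − po) / (n(1 − pe)²)], with n = 40 and categories 20/30/50%, so pe = 0.04 + 0.09 + 0.25 = 0.38.

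- Kappa 0.40: po = 0.628, half-width 0.24.
- Kappa 0.60: po = 0.752, half-width 0.22.

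For a blinded kappa of 0.40, the bias in step 2 equals the half-width when c × 0.60 = 0.24, that is, when c is about 40%.

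**The case against.** The strongest reply is that kappa is not computed from the investigators' check at all. It compares clusters with categories from faculty who assess students in routine teaching, and no section says that these faculty verify alerts. Table 7 does claim independence, and its object is risk status rather than the AI output. Records are coded, and the text after Figure 1 limits the linkage file to the principal investigator and a data steward. The outcome is exploratory, the statistical sections rule out validity claims, and rating order and forms may sit in a fuller protocol or in the workflow figure, which is not visible.

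Much of this stands, and it rules out three stronger readings that a reader might infer:

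- *Agreement is inflated by design because the same people do both tasks.* This overlap is stated for the investigators' manual evaluation. It is not shown for the faculty assessors behind kappa.
- *Kappa must be near 1 by construction.* That needs the same cut-offs on the same scores. The AI side of the planned kappa is unsupervised clustering without preset labels, which need not match faculty categories even on shared data. Table 2 is a sample for the supervised model, and nothing says that faculty recompute it.
- *By week 10 every rater knows who was flagged at week 5.* The document supports only that mentors may know: they are notified, and the Statement for data privacy gives the mentor a pass key.

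The reply does not remove the point. The article itself gives investigators both tasks and names mentor ratings as a comparator while mentors approve the messages. That is a stated overlap, not detail lost in condensation. Nor do the disclaimers settle it, since Data processing speaks of confirming accuracy and the main Discussion of validating the model.

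**Conclusion.** The concern holds in a limited form. As written, the plan allows human raters to see the AI output before or while they rate, and lets rubric scores enter the AI side. Percentage agreement and kappa may therefore be biased upward.

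The size cannot be derived from the document. The figures above rest on assumed category frequencies, reliabilities, blinded kappas and take-over shares. They show only that a bias comparable with the sampling error at n = 40 is possible under such assumptions.

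Shared data are not a fault if the aim is merely to see whether the AI reproduces a mentor's view; they become one when agreement is read as accuracy or validity. Severity is moderate: the primary feasibility and acceptability outcomes are not affected.

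**What to change.** 1. At weeks 5 and 10, have the faculty rater record and lock each student's category, with a time stamp, before any AI label or alert is released to that rater. Compare it with the raw AI label, stored before any mentor edit.
2. Make week 5 the main agreement analysis and week 10 supportive, because mentors may by then know the week-5 flags.
3. State who assigns the reference category and from which data. If it is a recomputation from the Table 2 cut-offs, report it only as a processing check.
4. Reconcile the Abstract's Discussion, Data processing, the Interpretation framework, the main Discussion and Table 7 on who rates and how independently. Do not describe the agreement result as accuracy or validation.
5. Optionally, add a descriptive table of AI label against the end-semester exam result. This works only if the exam component can be separated from the 65 continuous-assessment points; the final score named as the third assessment may contain them. Mentoring given in between can weaken the association.

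The cost is a small change in workflow order and a time-stamped form, plus one table if the optional step is taken. Step 1 removes the review bias at week 5 and limits it at week 10. It does not remove the effect of shared inputs, which has to be disclosed through step 3.

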**Figure 1 F1:**
[figure not shown]
Overview of the intended workflow.

Student names and contact details remain entirely within existing institutional systems and are never exposed to the AI-assisted system. The system operates on pseudonymized records, using coded identifiers to generate risk labels and draft support messages. Any messages produced are reviewed by staff and, if approved, are delivered through the learning management system or institutional email, ensuring that all student communication occurs within established, secure channels.

Operationally, analysis is conducted on a dataset containing only coded identifiers and learning-related features, while the file linking these codes to student identities is stored separately in an encrypted location. Access to this linkage is restricted to the principal investigator and a designated data steward. The identity key is retained only as long as necessary to support the intervention and is deleted after final grades are released; there is an additional predefined retention period, in line with institutional data governance requirements.

We design the intervention to focus on practical, short-term learning behaviors on which students could realistically act, rather than on generic study advice. Revised messages are grounded in self-regulated learning theory and guide students to set a clear goal for the next 7–10 days, take one or two concrete actions tied to specific course assessments (such as reviewing feedback or practicing a particular skill), and reflect briefly on progress. Each message also provides an explicit invitation to connect with a mentor through office hours or a scheduling link. All along, the tone emphasizes support and next steps, while avoiding deficit-based or stigmatizing language.

To ensure that the approach is feasible and safe in practice, we simplify the workflow and add clear human oversight. Messages are generated from standardized data extracts using a small library of templates, keeping instructor effort manageable. When used, AI support is limited to improving clarity and tone within these templates; all messages are reviewed and approved by a mentor before being sent. We also introduce an escalation pathway so that students showing sustained disengagement or significant performance decline are referred to human support in line with institutional procedures, reducing the risk of harm from false positives or misclassification.

### Data privacy

In this data analysis process using CHATGPT, student identifiers and contact details remain within institutional systems. The AIAS outputs risk labels and message drafts using pseudonymized records. Messages are sent via learning management system (LMS)/institutional email systems after staff review to ensure confidentiality, privacy, and protection from mishandling by fraudulent sources.

### Statistical analysis

Statistical analyses were conducted in alignment with the pilot and exploratory objectives of the study, with clear separation between primary implementation outcomes and secondary analytic agreement outcomes. No analyses were intended to establish diagnostic accuracy or predictive validity.

#### Analysis of primary outcomes

Descriptive statistics were used to summarize feasibility and acceptability outcomes derived from student and faculty surveys and system-usage metrics. Continuous variables were reported as means and standard deviations or medians and interquartile ranges, as appropriate. Categorical variables were summarized using frequencies and percentages. Likert-scale responses were analyzed descriptively and, where relevant, collapsed into agreement categories to facilitate interpretation. Open-ended responses were analyzed using thematic content analysis, with themes reported narratively to contextualize quantitative findings.

#### Analysis of secondary outcomes

Secondary analyses focused on exploratory agreement between AI-derived student clusters and faculty assessments. AI outputs were treated as unsupervised groupings, without prespecified performance labels. Agreement between AI cluster membership and faculty-assigned performance categories was examined using (1) confusion matrices, (2) percentage agreement, and (3) Cohen's Kappa, with 95% confidence intervals

Given the limited sample size, Kappa values were interpreted cautiously, emphasizing direction and magnitude rather than threshold-based validity claims.

#### Resampling and stability assessment

To assess the stability of observed agreement patterns, resampling-based techniques were employed where applicable. Repeated stratified k-fold cross-validation was used to examine the consistency of clustering–assessment alignment across different data partitions. These procedures were not intended to optimize model performance but to evaluate robustness under data perturbation. The results from resampling analyses were summarized descriptively, and variability across folds was reported to reflect uncertainty inherent in small-sample modeling.

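### The spread across cross-validation folds is presented as small-sample uncertainty, but it does not estimate the uncertainty of cluster–faculty agreement at n=40

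*Protocol article*

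**What the plan says.** Under Resampling and stability assessment, the protocol article states: "Repeated stratified k-fold cross-validation was used to examine the consistency of clustering–assessment alignment across different data partitions". It gives the purpose as follows: "These procedures were not intended to optimize model performance but to evaluate robustness under data perturbation". Results are to be summarised descriptively, and "variability across folds was reported to reflect uncertainty inherent in small-sample modeling".

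Other sections also deal with uncertainty:

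- Analysis of secondary outcomes lists "1) confusion matrices, (2) percentage agreement, and (3) Cohen's Kappa, with 95% confidence intervals". Secondary outcomes: analytic agreement also attaches 95% intervals to kappa.
- Sample size and power considerations says that confidence intervals on the agreement statistics convey sampling variability.
- Data processing, speaking of model evaluation at n=40, names "repeated stratified k-fold cross-validation (or leave-one-out CV) and bootstrap confidence intervals to reduce instability from fixed splits".

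The article does not give the number of folds or repeats. It also does not say whether agreement is computed in the held-out fold or in the part that remains.

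**The concern.** The clause on fold variability gives the fold spread an inferential meaning: it tells the reader how uncertain the result is with so few students. The spread of a statistic across folds answers a different question, and its size is set largely by the number of folds.

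- A held-out fold contains a handful of students, so the spread describes agreement in samples of that size, not in 40.
- The training parts share most of their students, so their spread is small by construction. Two 10-fold training sets have 32 of 36 students in common, and two 5-fold sets have 24 of 32.

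Neither spread is the standard error of kappa in 40 students. The report would then carry two measures of uncertainty for the same statistic, one of them mis-scaled. The article intends these results to inform larger confirmatory studies, so a misread precision could carry forward into their design.

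**Working it through.** **Inputs.** n=40 is from Data processing. The article states no k, number of repeats, kappa or standard error (SE), so there is no figure of its own to reproduce. The following are assumptions: k=5 or 10, 10 repeats, true kappa 0.4, 0.6 or 0.8, and category shares of 25/35/40%, 30/70% or 15/85%.

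**Closed form.** For a statistic that behaves like a mean, with SE denoting its standard error in all n students and d = n/k students held out:

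- SD across held-out folds ≈ SE × √k
- SD across training parts ≈ SE × √(d/(n−d))

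| k | Held out | Held-out SD / SE | Training-part SD / SE |
|---|---|---|---|
| 5 | 8 | √5 = 2.24 | √(8/32) = 0.50 |
| 10 | 4 | √10 = 3.16 | √(4/36) = 0.33 |
| 40 (leave-one-out) | 1 | √40 = 6.32 | √(1/39) = 0.16 |

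**Simulation.** There were 600 data sets per scenario, with cluster labels held fixed. Each entry is the average fold SD divided by the true sampling SD at n=40, as a range over the nine scenarios.

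| Statistic | k | Held-out | Training part |
|---|---|---|---|
| Kappa | 5 | 1.79–2.08 | 0.46–0.52 |
| Kappa | 10 | 2.15–3.22 | 0.32–0.35 |
| Percentage agreement | 5 | 1.83–2.05 | 0.46–0.51 |
| Percentage agreement | 10 | 2.77–3.11 | 0.31–0.35 |

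A separate check with shares of 50/35/15% and kappa 0.6 gave ratios for kappa of 1.9 (k=5) and 3.0 (k=10) held-out, and 0.47 and 0.32 in training parts.

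**One scenario in absolute terms** (25/35/40%, kappa 0.6). The true SE of kappa is 0.103, a half-width of 1.96 × 0.103 = 0.20. If the fold SD were read as an SE:

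- Held-out, k=5: 2.08 × 0.103 = 0.21, half-width 0.42.
- Held-out, k=10: 3.17 × 0.103 = 0.33, half-width 0.64.
- Training part, k=5: 0.52 × 0.103 = 0.054, half-width 0.11.
- Training part, k=10: 0.35 × 0.103 = 0.036, half-width 0.07.

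**Small folds.** With 15/85% shares, held-out kappa could not be computed in 4–7% of 5-fold folds and 28–35% of 10-fold folds.

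**Leave-one-out.** With one held-out student, kappa is (1−1)/(1−1) = 0/0 if the two labels agree and (0−0)/(1−0) = 0 if they differ, so it carries no information. Percentage agreement is 0 or 1 per fold and does have an SD, about 5.9 to 6.5 times the SE. Training-part values also exist, at 0.15 to 0.17 times the SE.

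**Limit of the check.** Clustering was not refitted in each fold. Refitting would add variability not counted here.

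**The case against.** The strongest objection is that the plan already reports proper uncertainty. Kappa has 95% intervals, the sample-size section gives those intervals the task of showing sampling variability, and Data processing names bootstrap intervals. The resampling section calls its output descriptive, and the agreement analysis is secondary and exploratory with no validity claim. All of this stands, and it limits the point to the fold-based figure. It does not remove the point, because the sentence still says what that figure reflects, and on neither reading is that so.

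Several stronger readings are tempting but not supported by the article:

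- **That all error bars on agreement are wrong.** The declared error bars are the confidence intervals.
- **That leave-one-out is the planned measure for cluster agreement.** It appears only in Data processing, for model evaluation and alongside bootstrap intervals. It makes only held-out kappa uninformative; the other statistics remain computable, though badly scaled.
- **That averaging over repeats yields a spuriously small standard error.** The SD of repeat means would indeed be only 0.04 to 0.21 of the SE, but the article nowhere announces such a figure.
- **That the section fails its purpose by not testing the clusters.** Its purpose is the stability of agreement. A cluster-stability index would be a useful addition, not a stated target that is missed.
- **That stratifying on faculty categories contradicts label-free clustering.** Labels used to form partitions for an agreement analysis are not fed to the algorithm.

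The unstated k and number of repeats are details that an article may leave to the full plan, and they are not held against it.

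**Conclusion.** The point holds in a narrow form. Reported as the uncertainty of cluster–faculty agreement at n=40, fold variability is mis-scaled on either reading: roughly 2 to 3 times too wide from held-out folds, or 2 to 3 times too narrow from training parts. That size rests on k=5 or 10 and fixed cluster labels. It changes little over the kappas and category shares tried, and most of it follows from k alone. For the leave-one-out option the factor is about 6, and held-out kappa is uninformative. The primary feasibility and acceptability outcomes are untouched, and so are the planned confidence intervals. What needs correcting is one stated interpretation, which would otherwise put a second, conflicting precision figure beside those intervals.

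**What to change.** In Resampling and stability assessment, stop presenting fold variability as uncertainty. Either label it descriptive stability only, or drop it.

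Take the uncertainty of percentage agreement and kappa from one bootstrap over students, the type of interval that Data processing already names. Scaling, clustering and any cluster-to-category mapping should be re-run in each resample. The same resamples can optionally give an adjusted Rand or Jaccard index if cluster stability is of interest.

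For any supervised model, use cross-validation to obtain one out-of-fold label per student. Compute a single pooled kappa on the 40 labels rather than a kappa per fold.

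The cost is a few sentences and minor extra compute, with no additional data. Intervals may be somewhat wider, because the bootstrap also counts the variability of the clustering itself.
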